### Secondary Outcome

The secondary outcomes include an improvement in the severity of anxiety symptoms (evaluating at the HAM-A), of global functioning and personal functioning (evaluated at the CGI and at the GAF, respectively), an improvement in family members' coping strategies (i.e., an improvement in “problem-oriented” strategies reduction); in the level of quality of life (evaluated at the MANSA) and of family functioning.

## Discussion

Pregnancy is a stressful period for women, which can be further complicated by an early postnatal hospital discharge (85, 86). Risk factors for PD include previous mental disorders, low socioeconomic status, being a single mother, general life stress (12), unwanted and unplanned pregnancies (22), conflicts with the partner, lack of support, limited information, and stigma (87).

Despite many scientific associations and task forces, including the United States' Preventive Services Task Force (USPSTF) (88), the National Institute for Health and Care Excellence (62), the Canadian Task Force on Preventive Health Care (CTFPHC) (89) and the American College of Obstetricians and Gynecologists (68), have highlighted the importance of developing screening and treating programs for PD, there are still many unsolved issues, such as efficacy and the availability of those programs, whose efficacy has been demonstrated by RCTs.

One of the main strengths of our study is represented by the adaption of a well-known family psychoeducational model to the treatment of perinatal depression. In particular, the Falloon psychoeducational intervention was developed for the community management of schizophrenia (63, 90) and has been subsequently adapted to the management of major depression (59, 91) and bipolar disorder (57, 92–94). Perinatal depression may represent an ideal target for this kind of interventions, since it is highly dependent from stressful life events and from family context. Moreover, peripartum is a period of women's life in which pharmacological treatments should be used very cautiously and only in a limited situations. Another strength of our study is the rigorous methodology adopted, which will allow us to understand the impact of the experimental intervention on patient's outcome through a randomized controlled approach. Moreover, the main outcome is the reduction of depressive symptoms at 3-months after randomization. This is an ambitious outcome, since many confounding variables can impact on it. In particular, in some cases the childbirth represents itself an event associated with a reduction of depressive symptoms (95), thus biasing the effectiveness of the experimental intervention. Moreover, other contextual factors (such as support by family members, changes in the daily routine following the childbirth, or starting a pharmacological treatment) can have an impact on the long-term outcome. We aim to control for such variables using a statistical procedure, in order to accommodate for the impact of all these confounding variables.

Furthermore, the postnatal psychoeducation programme is suitable for clinical use as it is relatively brief and can be delivered by postnatal unit nurses and midwives after a short period of training.

Another strength of this study is the use of the EPDS as screening measure, which will allow comparisons with data from other international studies.

In order to detect patients affected by both major and minor depression, the cut-off at EPDS of ≥10 has been selected (71) and it will have to be complemented by the clinical judgment (96).

The assessment tools have been selected on the basis of their wide use in clinical practice and in clinical trials (84). Therefore, the adoption of these instruments will give us the opportunity to compare our findings with those of other previous studies. Moreover, the HAM-A and HAM-D are well-known, validated, reliable, and easy to use scales, and have been selected in order to not overburden the researchers and mental health professionals involved in the study with a specific training on the use of assessment tools (84).

Our study has some limitations. The first is the fact that the study will be carried out in one center only, with a consequent reduced generalizability of findings. However, this can be considered as a pilot study representing the basis for a larger multicentric study that our research group is planning.

Another possible limitation is the exclusion from the study of women with psychotic disorders or women with depressive disorders before pregnancy. This methodological choice was due to the need to assess and treat only patients with an onset of depression during pregnancy. Another possible limitation is the lack of a standardized pharmacological treatment for women that will be recruited for the RCT phase. Despite a standardized pharmacological treatment could be useful to assess more precisely the efficacy of the experimental psychoeducational intervention, we decided not to standardize the pharmacological treatment in order to treat women with PD under ordinary conditions. In any case, the pharmacological management of pregnant women will follow the NICE guidelines (62).

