## Aims

The present trial aims to evaluate the efficacy and feasibility of a new psychoeducational family intervention compared to the Best Treatment Option (BTO) in a sample of women affected by perinatal depression and their family members. The Best Treatment Option (BTO) is provided according to the NICE guidelines (62). In particular, mild to moderate forms of depression may be addressed with self-help or psychological counseling. For moderate or severe forms of PD, high-intensity psychological intervention, or pharmacological treatments are recommended.

The secondary aims are to: (1) improve mental health literacy on the topic of perinatal depression, with a specific focus on risk and protective factors as well as on available therapeutic strategies for the management of perinatal depression; (2) identify clinical, socio-cultural, and pregnancy-related predictive factors for the development of perinatal depression; (3) improve coping strategies and family functioning of family members participating to the intervention; (4) evaluate the long-term effects of the intervention.

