The Edinburgh Postnatal Depression Scale (EPDS) (64) is a simple and short 10-items self-report screening questionnaire initially developed for use in postnatal women to improve detection of postnatal depression. The EPDS allows health professionals to detect women who might need help and require a referral for a full diagnostic assessment. EPDS has satisfactory sensitivity and specificity values and it is also sensitive to changes in severity of depression over time. For the purpose of the present study, the cut-off threshold has been set at ≥ 10 (66). In validation studies, different cut-off points have been found due to clinical, social, cultural and economic diversities (70). The cut-off score for possible depression (i.e., a positive screening result) is ≥13 points but, as suggested by Hewitt et al. (71), a cut-off score ≥ 10 can be used in order to identify patients with both major or minor depression. Moreover, given the observed variability in the performance of the test, the screening procedure could produce both false positives and negatives (72). Therefore, it is essential that this screening tool is complemented by the clinical judgment (73).The Hamilton Depression Rating Scale (HAM-D) (74) is a 17-items questionnaire used to rate the severity of depressive symptoms such as low mood, insomnia, agitation, anxiety and weight loss. The interview and scoring take about 15 min. The score for each item ranges from 0 (not present) to 4 (extreme severity).The Hamilton Anxiety Rating Scale (HAM-A) (75) is a 14-items questionnaire developed to measure the severity of anxiety symptoms, both psychic anxiety (mental agitation and psychological distress) and somatic anxiety (physical complaints related to anxiety). The score for each item ranges from 0 (not present) to 4 (extreme severity).The Global Assessment of Functioning (GAF) (76) is a 100-point rating scale assessing social, occupational, and psychological functioning of adults, with higher scores indicating better level of functioning.The Clinical Global Impression (CGI) (77) scale measures illness severity (CGI-S), global change (CGI-C) and therapeutic response. The CGI-S is rated on a 7-point scale, from 1 (normal) to 7 (the most severely ill patients). The CGI-C scores range from 1 (very much improved) to 7 (very much worse). Treatment response ratings should take into account both the therapeutic efficacy and the treatment-related adverse events, and range from 0 (marked improvement and no side-effects) to 4 (unchanged or worse, and side-effects outweigh the therapeutic effects). Each component of the CGI is rated separately; the instrument does not provide a global score.The Manchester Short Assessment of Quality of Life (MANSA) (78) is a 17-item questionnaire assessing quality of life focusing on satisfaction in twelve aspects of life. For twelve items, the satisfaction is rated on 7-point rating scales, ranging from 1 (“could not be worse”) to 7 (“could not be better”). For five items, the responses are binary (“yes” or “no”). The total MANSA score is the mean of the Likert-item scores.The Family Assessment Device (FAD) (79), based on the McMaster Model of Family Functioning, consists of 7 subscales on family involvement in patient's care (affective involvement, affective responsiveness, behavioral control, communication, problem solving, and roles and general family functioning). Scores range from 1 (“healthy functioning”) to 4 (“unhealthy functioning”).The Family Coping Questionnaire (FCQ) (80) is a self-administered 34-items questionnaire, which has shown a good reliability and external validity. Each item is rated on a 4-level scale, from 1 (“never”) to 4 (“always”). The items are grouped into the following 11 subscales: information on patient's illness; positive communication toward the patient; relatives' maintenance of social interests; patient's involvement in social activities; talking with friends about the patient's condition; coercion; avoidance; resignation; use of alcohol and drugs; collusion; search for spiritual help. The FCQ is widely used for the assessment of coping strategies among relatives of people with severe mental disorders (81, 82).The Pattern of Care Schedule (PCS) (80), a 40-item questionnaire on pharmacological and non-pharmacological treatments as well as on health care access made by the patient. It is compiled by the researcher in collaboration with the patient. If information is inadequate, or if the researcher is not sure about patients' reliability, other sources (e.g., treating physician, relatives, etc.) can be consulted. During the study period, the treating clinician will continue to provide the usual treatment to patient, and–if necessary–to change or adjust the pharmacological regimen. This schedule is used in order to record pharmacological treatments and doses, psychotherapeutic and psychosocial interventions (type of intervention, number of sessions) provided to patients in order to document the BTO.

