### Data Analysis

Differences in socio-demographic and clinical characteristics, such as severity of depressive and anxiety symptoms, quality of life, trimester of pregnancy, and personal functioning between the two groups will be evaluated using Chi-square or *T*-test for independent samples, as appropriate. Differences in coping strategies and in family accommodation reported by relatives will be evaluated with the same tests.

In order to assess the efficacy of the experimental intervention, a linear multivariable regression model will be implemented, using as main outcome the score at HAM-D at 3 months post-randomization. Moreover, several confounding variables (such as age, marital status, familiarity for mental disorders, peer support, previous pregnancy, etc.) will be entered in the model. Furthermore, predictors of response at the end of the intervention will be identified.

“Response” is generally defined as a 50% decrease in scores on Hamilton Depression Rating Scale (HAMD) (74). In this protocol, we will consider the score at the 3-month HAM-D compared with the baseline score. Therefore, the continuous variable “3-month HAM-D score” will be transformed in a binary variable (1 = response; 0 = absence of response), and it will be entered in a logistic regression multivariate model in order to identify possible predictors of positive response to the experimental intervention.

In order to evaluate differences in relatives' coping strategies according to patients' clinical features and type of relationship with the patient, a two-level model with fixed independent variables and random intercept, using a maximum likelihood estimation, will be performed. The mean score at the subscales of the FCQ will be entered in the model, adding covariates step by step in order to identify the model with indexes of best fit. The final model will be selected according to the−2 loglikelihood value, and the model with the lowest value will be choose. Estimate, standard error, 95% confidence interval, and *P*-values will be calculated.

The level of significance will be set at *p* < 0.05. All analyses will be performed using the Statistical Package for Social Science software (SPSS), version 18.0 (SPSS).

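### The intention to control for confounders that can arise after randomisation, with a covariate list not limited to baseline, could distort the treatment effect in either direction

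*Protocol article*

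**What the plan says.** For efficacy, Data Analysis states that "a linear multivariable regression model will be implemented, using as main outcome the score at HAM-D at 3 months post-randomization". It adds that "several confounding variables (such as age, marital status, familiarity for mental disorders, peer support, previous pregnancy, etc.) will be entered in the model". No time point is given for these covariates, and the list ends in *etc.*

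The Discussion returns to the 3-month outcome and describes what might bias it. It says that "in some cases the childbirth represents itself an event associated with a reduction of depressive symptoms". It then lists contextual factors, "support by family members, changes in the daily routine following the childbirth, or starting a pharmacological treatment", that may affect the long-term outcome, and closes with "We aim to control for such variables using a statistical procedure, in order to accommodate for the impact of all these confounding variables". Nothing labels this control as a sensitivity, mediation or exploratory analysis.

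Other sections bear on whether the intervention can change these factors:

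- A secondary aim is to "improve coping strategies and family functioning of family members participating to the intervention". Secondary Outcome includes relatives' coping and family functioning.
- Features of the Experimental Intervention describes modules on communication and problem solving. The second module covers drug and non-drug options and adherence.
- During the study, "the treating clinician will continue to provide the usual treatment to patient, and–if necessary–to change or adjust the pharmacological regimen" (description of the Pattern of Care Schedule, PCS).

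**The concern.** Randomisation removes confounding of the comparison by anything fixed before allocation, apart from chance imbalance. A factor that arises afterwards cannot confound allocation. It can lie on the path from allocation to outcome, or share causes with the outcome. Conditioning on it then replaces the effect of being allocated to the intervention with a partial effect, which has a causal meaning only under further assumptions about unmeasured common causes.

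Two of the named factors are exposed to this. Family support is close to what a family intervention sets out to improve. Starting a drug can respond to the content of the second module and to how the woman is doing. At stake is the main efficacy estimate at 3 months, which the article presents as the product of a randomised design.

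**Working it through.** **1. The plan's own figure.** Power Analysis gives effect size 0.65, α 0.05, power 0.95 and 1:1 allocation. A two-sided two-sample t-test needs 62.49 per arm, so 63 per arm and 126 in total. The normal approximation, 2(1.960 + 1.645)²/0.65² = 61.5, gives 62 per arm and 124. The stated 126 reproduces, and power at 63 per arm is 0.952. The sample size is not at issue.

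**2. Timing of each named factor, and whether the arm can affect it.**

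- *Starting a drug:* it can occur after randomisation, because treatment may change during the study. The arm can plausibly affect it.
- *Support by family members:* no time point is stated. A T0 value is a proper covariate; a later value can be affected by the arm.
- *Routine changes after birth:* these come after randomisation for women who enter while pregnant.
- *Childbirth:* timing is largely set by gestational age at entry. For women enrolled within 3 days of delivery (Inclusion Criteria) it is already a baseline fact. The arm is unlikely to affect it.

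**3. What adjustment does to the coefficient.** Let A be the arm, M the later factor (within-arm SD 1), Y the HAM-D in SD units, and τ = −0.65 the total effect. Let a be the effect of A on M, and b the effect of M on Y.

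- With no other common cause, the adjusted coefficient is τ − ab.
- With an unmeasured common cause U (SD 1) that affects M by c and Y by e, it is τ − a(b + ce).

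All path sizes below are assumptions, and drug starting is treated as a continuous variable for simplicity.

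- *Support raised by the intervention,* a = 0.5, b = −0.4: −0.65 + 0.20 = −0.45. With c = −0.4, e = 0.5: −0.65 − 0.5(−0.6) = −0.35.
- *Drugs started less in the experimental arm,* a = −0.5, b = −0.3: −0.65 − 0.15 = −0.80. With c = 0.4, e = 0.5: −0.65 + 0.5(−0.1) = −0.70.
- *Factor not affected by the arm,* a = 0: −0.65, unchanged.

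A simulation with 1,000,000 records gave −0.452, −0.349, −0.801, −0.700 and −0.649 for these five cases. The direction therefore depends on which factor is entered and how the arms differ on it. If the total effect were zero, the first drug case would still give 0 − 0.15 = −0.15.

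**4. Illustration of lost power.** If a share m of the effect is adjusted away, d = 0.65(1 − m). Two-sided t-test, 63 per arm:

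| m | d | Power | Total N for 95% power |
|---|---|---|---|
| 0% | 0.65 | 0.952 | 126 |
| 10% | 0.585 | 0.903 | 154 |
| 20% | 0.52 | 0.825 | 196 |
| 30% | 0.455 | 0.717 | 254 |
| 40% | 0.39 | 0.584 | 344 |
| 50% | 0.325 | 0.440 | 496 |

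These powers use the unadjusted SD. A covariate that predicts HAM-D also lowers residual variance. For a = 0.5, b = −0.4, unit within-arm SDs and no common cause, the residual variance is 1 − 0.16 = 0.84, and the share of the variance of A not explained by M is 1/1.0625 = 0.941. The standard error is √(0.84/(126 × 0.25 × 0.941)) = 0.168, and 0.45/0.168 = 2.67. Power is then about 0.76, against 0.71 for an unadjusted test at d = 0.45. The table slightly overstates the loss in such a case.

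**The case against.** The strongest reply is that the operative text is Data Analysis, and most covariates named there (age, marital status, family history, previous pregnancy) are baseline facts. None of the Discussion's factors appears in it. The Discussion sentence states an intention, names no model, and ties the contextual factors to the long-term outcome rather than to 3 months. Only the *etc.* joins the two places. This stands in part: the article does not show that these factors will be in the 3-month model. But it does say they will be controlled for, in a paragraph that opens on the 3-month result, and no rule keeps them out. A comparison of arms at a later visit would have the same problem.

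Other parts of the reply stand in full:

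- Family support could be taken at T0. The Family Assessment Device (FAD) is scheduled then, and Baseline Assessments records the partner relationship and family conflicts.
- Adjusting for childbirth timing does little harm.
- Peer support, named in Data Analysis, is weak evidence. Peers are not a stated target of a single-family intervention, and its absence from Table 3 of a condensed article does not show that it is measured after randomisation.

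A reader might infer that the adjustment must shrink the effect. The documents do not support that: if the intervention reduces drug starts and drugs lower HAM-D, adjusting for them enlarges the apparent benefit.

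**Conclusion.** The point holds in a limited form. The article declares an intention to control for factors that can arise after randomisation and can be changed by the intervention: starting a drug and, if measured after T0, family support. Its efficacy model has no baseline restriction to prevent this. If they were entered, the coefficient would no longer estimate the effect of allocation, and the distortion could go either way.

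The size cannot be derived from the article. The range of −0.35 to −0.80 around a total effect of −0.65, and the fall in power from 0.95 to about 0.82-0.72 when 20-30% is adjusted away, rest wholly on assumed path sizes. A reader might also conclude that the plan already commits the primary analysis to adjusting for all post-randomisation events. That goes further than one Discussion sentence and an open list allow.

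**What to change.** In Data Analysis, state that the efficacy model uses only prespecified covariates measured at or before T0, and replace *etc.* with a closed list. Candidates already scheduled at T0 are HAM-D, gestational period or postpartum status, FAD and medication from the PCS. State when peer support is measured, or leave it out.

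In the Discussion, reword the sentence on confounders to match. Gestational period or postpartum status at T0 deals with delivery timing. Report later drug starts, family support and routine changes by arm, or use them only in an analysis labelled exploratory.

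The cost is wording, settled before the data are analysed. The suggested baseline measures are already collected, and the sample size stays at 126 with power 0.952 for the planned effect of 0.65.

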## Conclusions

Perinatal depression represents a serious threat for mental health, also considering the detrimental consequences for children. Therefore, it is an ethical imperative to identify new strategies for adequately treat such conditions and reduce the long-term negative impact on the mothers as well as their babies and family members. We hope that the study we will carry on will help to improve the clinical, psychosocial, and family management of perinatal depression.
